#### Secondary study parameters

For secondary outcome measures, between-group differences will be analyzed using independent samples *t*-tests, chi-square test, or Mann-Whitney tests, where appropriate and adjusted for center and ECMO mode. If necessary, multivariable regression analysis will be used to adjust for imbalances in main prognostic variables between the intervention and control groups.

#### Other study parameters

##### Cost-effectiveness analyses

The difference in costs for use of heparin and aPTT measurements will be neglectable. Cost-effectiveness will be based on reduced costs of blood transfusions and interventions for bleeding as well as improved outcome. All medical cost items expected to be affected by the ECMO therapy will be measured and valued according to the Dutch and Belgium standard guidelines for economic evaluations, e.g., blood transfusion, number of ECMO replacements, surgery, and hospital length of stay. Health gains will be measured in terms of quality-adjusted life-year (QALY) based on EQ-5D-5L-defined utilities. The Budget Impact Analysis (BIA) will be performed from a healthcare perspective to inform decision-makers about the financial consequences of reduced anticoagulant targets in ECMO treatment in Dutch and Belgium healthcare. The model will take changes in the availability and adoption of the reduced anticoagulant targets into account by calculating the financial consequences of five scenarios with a time horizon of 5–10 years.

### Interim analyses {21b}

An unblinded interim analysis will be performed when the first 150 patients have been enrolled in the study. An independent statistician will perform this analysis and the results will be presented to the safety committee. The commission will calculate the power for non-inferiority, conditioned on the difference between treatments concerning outcome rates and on the non-inferiority margin of 7.5%. If the conditional power is 50–79%, the sample size will be re-estimated to maintain a conditional power of 80%.

If the difference between the treatment groups will be significant at an alpha level of 1%, the trial will be stopped because of “proof beyond reasonable doubt” that intervention treatment is non-inferior to standard treatment.

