### Sample size {14}

We expect that with a target of 1.5–2.0× baseline aPTT or with LMWH the primary composite endpoint will be reached in 60% of patients compared to 70% in usual care. To show non-inferiority with a significance level (alpha) of 5%, power of 80%, and a non-inferiority limit (delta) of 7.5%, the corresponding sample size is 91 patients per group. In other words, if there is a true difference in favor of the experimental treatment of 10%, then 91 patients per group are required to be 80% sure that the upper limit of a one-sided 95% confidence interval (or equivalently a 90% two-sided confidence interval) will exclude a difference in favor of the standard group of more than 7.5%, thus 75.25% in the intervention groups compared to 70% in usual care. To compensate for a lower effect and drop-outs, 330 patients will be enrolled. Drop-outs are defined as the withdrawal of informed consent or loss to follow-up.

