### Composition of the data monitoring committee, its role and reporting structure {21a}

The study is considered a low-risk study and therefore we have appointed a safety committee instead of a Data Monitoring Committee (DMC) to perform interim analyses for safety, futility, or positive efficacy so that the steering committee can remain blinded for the outcome of the study. All the members have no conflict of interest with the sponsor of the study.

The Safety Committee will:

Monitor recruitment figures and losses to follow-upMonitor evidence for treatment harmMonitor overall conduct and data quality, including completeness, encouraging collection of high-quality dataMake recommendations that the trial continues to recruit participants or whether recruitment should be terminated either for everyone or some treatment groups and/or some participant subgroupsPerform the pre-planned interim analysis and recommend the continuation of the study accordinglySuggest additional data analysesGive uncalled-for recommendations based for example on data from recently presented studiesGive uncalled-for recommendations if the assumptions made for the sample size calculation of the study prove to be incorrect. The assumptions may pertain to patient accrual and the incidence of the primary outcome event.

The executive committee will send a safety report to the safety committee once every 3 months. The advice of the safety committee will be sent to the sponsor of the study and the reviewing Medical Research Ethics Committee (MREC).

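### The interim stopping rule concludes non-inferiority from a significant difference at 1%, without naming the 7.5-point margin, the direction, the sidedness or the contrast

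*Protocol article*

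**What the plan says.** Under *Interim analyses {21b}* the protocol article plans one look: "An unblinded interim analysis will be performed when the first 150 patients have been enrolled in the study". An independent statistician reports to the safety committee. Two things follow from the look.

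- **Conditional power.** Power for non-inferiority is calculated "conditioned on the difference between treatments concerning outcome rates and on the non-inferiority margin of 7.5"%, and "If the conditional power is 50–79%, the sample size will be re-estimated to maintain a conditional power of 80"%. Here the margin is named.
- **Stopping.** "If the difference between the treatment groups will be significant at an alpha level of 1%, the trial will be stopped because of" what is described as conclusive proof "that intervention treatment is non-inferior to standard treatment". Here the margin is not named, and neither are a direction, one- or two-sidedness, or a pair of arms.

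The trial has three arms, and *Statistical methods for primary and secondary outcomes {20a}* compares the confidence interval for each intervention arm with the 7.5% margin, using a 95% interval. *Sample size {14}* works with a one-sided 95% limit. Neither section mentions an allowance for the interim look. The section on the data monitoring committee {21a} sets up the safety committee "to perform interim analyses for safety, futility, or positive efficacy", but gives no numerical boundary for harm.

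**The concern.** The criterion and the conclusion belong to different hypotheses. Non-inferiority is shown when the upper confidence limit for the excess risk (intervention minus usual care) lies below +7.5 points. A significant difference shows only that the excess is not zero, in whichever direction the data point. Four things are left open:

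1. whether zero or the margin is tested;
2. whether a result against the intervention counts;
3. whether 1% is one- or two-sided;
4. which contrast is meant, and whether the whole trial ends if only one intervention arm crosses.

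This is the only formal stopping criterion in the article. It is applied to unblinded data on a composite that includes death, and it can end the trial with a claim meant to change practice. A rule of this kind should give one answer for any data set, and this one does not.

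**Working it through.** **Inputs.** *Sample size {14}* states that "the primary composite endpoint will be reached in 60% of patients compared to 70% in usual care", with "significance level (alpha) of 5%, power of 80%, and a non-inferiority limit (delta) of 7.5%, the corresponding sample size is 91 patients per group". Total enrolment is 330, so 110 per arm at 1:1:1. The look at 150 enrolled gives about 50 per arm. I assume that all 150 have their 6-month outcome, use the unpooled normal approximation, and ignore sample size re-estimation.

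**The plan's own figure.** The variance term is 0.6×0.4 + 0.7×0.3 = 0.45, and the distance from the margin is 0.10 + 0.075 = 0.175. Then n = 0.45 × (1.645 + 0.842)² / 0.175² = 90.85, so 91 per group. The stated figure reproduces with one-sided 5% and an absolute margin of 7.5 points, which I therefore use throughout.

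**Direction favouring the intervention, at the planned rates.** SE = √(0.45/50) = 0.0949.

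| Interim rule | Observed benefit needed | Chance at 60% v 70% |
|---|---|---|
| Difference from zero, two-sided 1% | 2.576 × 0.0949 = 24.4 points | Φ(0.10/0.0949 − 2.576) = 6.4% |
| Non-inferiority, one-sided 1% | 2.326 × 0.0949 − 0.075 = 14.6 points | Φ(0.175/0.0949 − 2.326) = 31.5% |
| Non-inferiority, two-sided 99% interval | 2.576 × 0.0949 − 0.075 = 16.9 points | Φ(0.175/0.0949 − 2.576) = 23.2% |

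If the variance is recalculated at each boundary with usual care at 70%, the first two thresholds become 24.6 and 14.7 points.

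**Direction against the intervention, two-sided 1% against zero, usual care 70%.**

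- True rate 77.5% (+7.5 points): SE = √((0.21 + 0.1744)/50) = 0.0877; Φ(0.075/0.0877 − 2.576) = 4.3%.
- True rate 85% (+15 points): SE = √((0.21 + 0.1275)/50) = 0.0822; Φ(0.15/0.0822 − 2.576) = 22.7%.

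Exact binomial enumeration with a chi-square test gives 4.1% and 21.6%. The observed excess needed is about 20 points.

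**Type I error per contrast, at a true excess of 7.5 points.** I use a bivariate normal with information fraction 50/110 = 0.4545 and correlation √0.4545 = 0.674.

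| Interim rule | Final one-sided 5% | Final one-sided 2.5% |
|---|---|---|
| Zero-difference at two-sided 1%, only favourable results count | 5.00% | 2.51% |
| Zero-difference at two-sided 1%, harm also counted as non-inferior | 9.27% | 6.78% |
| Margin-based, one-sided 0.5% | 5.17% | 2.75% |
| Margin-based, one-sided 1% | 5.42% | 3.09% |

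To hold 5% per contrast, the final one-sided level would be 4.82% after a 0.5% interim or 4.55% after a 1% interim.

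**Both arms and both looks.** With the shared control (correlation 0.5 between contrasts), a one-sided 0.5% interim and a one-sided 2.5% final, the overall one-sided error is 4.99%. With a one-sided 1% interim it would be 5.6%.

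**The case against.** The strongest reply is that the intended meaning is clear. The preceding sentences tie the interim look to non-inferiority and the 7.5% margin, and the stopping sentence itself speaks of the intervention being non-inferior, which implies a direction. The results go to a safety committee that is charged with watching for treatment harm and may recommend ending recruitment for some groups. An article also condenses: alpha spending and the handling of each contrast may stand in the full protocol, the SAP or a charter.

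Much of this is fair. The committee would probably not declare non-inferiority from a harmful result; the 4% and 23% are chances of a significant harmful difference, not of anyone acting on it in that way. But the point is not missing detail. The article states a criterion and a conclusion that do not match, and no stated harm boundary overrides the literal reading.

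A reader might infer two stronger things that the documents do not support.

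- *That the rule can never justify its conclusion.* A difference favouring the intervention that is significant against zero also excludes +7.5 points. In that direction the rule is valid, only far too strict, and a missed early stop costs efficiency: the trial goes on to the margin-based final comparison.
- *That the rule as worded materially raises the type I error.* If only favourable results count, the error stays at 5.00% or 2.51%. The 5.4% and 3.1% belong to a margin-based interim test, which is not what the sentence says. Material inflation arises only if harmful results are counted as non-inferior.

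**Conclusion.** The stopping sentence is wrong as written and should be corrected. Its criterion is a difference from zero in an unstated direction for an unstated contrast, and its conclusion is non-inferiority. In the intended direction the cost is an over-strict rule: 24.4 v 14.6 observed points, and a 6% v 32% chance of stopping at the planned rates. In the other direction the literal wording attaches a non-inferiority conclusion to harm, with a crossing chance of about 4% at +7.5 points and 23% at +15; the practical risk is lower, because a committee sees the data.

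The final level is a secondary matter that arises once the interim look tests against the margin. If the 95% interval at the end is two-sided, no further adjustment is needed to stay within one-sided 5% across both arms and both looks when the interim uses a two-sided 99% interval. If the one-sided 5% of the sample size section governs, the excess per contrast is 0.2 to 0.4 points. The article does not settle which applies.

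The figures assume 50 per arm with complete 6-month outcomes. The trigger is enrolment, so fewer outcomes at the look would raise the thresholds. They also assume 70% events on usual care and no change of sample size after the look.

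**What to change.** Replace the stopping sentence, for example with:

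> For each intervention arm separately, non-inferiority at the interim is declared only if the upper limit of the two-sided 99% confidence interval for the risk difference (intervention minus usual care) is below +7.5 percentage points. A difference in favour of usual care never triggers this rule and goes to the safety committee as possible harm.

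Add one sentence saying whether the whole trial or only that contrast ends when one arm qualifies.

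Then state the final level to match. With a two-sided 95% interval per arm, keep it: both arms and both looks stay at about 5.0% one-sided, ignoring sample size re-estimation. If one-sided 5% is kept for each contrast, test at about 4.8% at the end; this holds the level per contrast, not across the two contrasts.

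The cost is a paragraph in the protocol, the SAP and the safety committee's charter, with negligible loss of power. *Trial status* reports 111 recruited, so at that point the rule could still be corrected before the look at 150.

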### Methods for additional analyses (e.g., subgroup analyses) {20b}

There will be no per protocol subgroup analysis. We will perform a comparison between the treatment groups adjusted for medical center and ECMO mode.

### Methods in analysis to handle protocol non-adherence and any statistical methods to handle missing data {20c}

Protocol violations will be reported in the investigator site files. The principal investigator will screen the eCRF regularly for missing data and will encourage local investigators to complete the eCRF. Nonadherence to the allocated treatment arm is possible as described at 11b; the subject will be analyzed as in the original treatment arm, according to the intention-to-treat principle.

### Plans to give access to the full protocol, participant-level data, and statistical code {31c}

The protocol of the study is publicly available on the website: https://ecmo-nl.com. The dataset generated during this study is available from the corresponding author upon reasonable request.

## Oversight and monitoring

### Composition of the coordinating center and trial steering committee {5d}

The principal investigator will have overall responsibility for the study and its management. The trial executive committee that consists of the principal investigator, project coordinator, research nurse, and data manager are all affiliated with the University Medical Center Groningen. They will be responsible for the day-to-day running of the trial. The trial steering committee will meet biannually or more often when needed. The study is part of the Dutch ECLS Study Group in which all Dutch ECMO centers are represented.

### Composition of the data monitoring committee, its role and reporting structure {21a}

The study is considered a low-risk study and therefore we have appointed a safety committee instead of a Data Monitoring Committee (DMC) to perform interim analyses for safety, futility, or positive efficacy so that the steering committee can remain blinded for the outcome of the study. All the members have no conflict of interest with the sponsor of the study.

The Safety Committee will:

Monitor recruitment figures and losses to follow-upMonitor evidence for treatment harmMonitor overall conduct and data quality, including completeness, encouraging collection of high-quality dataMake recommendations that the trial continues to recruit participants or whether recruitment should be terminated either for everyone or some treatment groups and/or some participant subgroupsPerform the pre-planned interim analysis and recommend the continuation of the study accordinglySuggest additional data analysesGive uncalled-for recommendations based for example on data from recently presented studiesGive uncalled-for recommendations if the assumptions made for the sample size calculation of the study prove to be incorrect. The assumptions may pertain to patient accrual and the incidence of the primary outcome event.

The executive committee will send a safety report to the safety committee once every 3 months. The advice of the safety committee will be sent to the sponsor of the study and the reviewing Medical Research Ethics Committee (MREC).

### Adverse event reporting and harms {22}

Clinical research involving critically ill patients illustrates several concerns with the existing system for monitoring adverse events.

Morbidity and mortality rates are high among patients in the ICU. In this particular study population, mortality rates exceed 50% [12]. Therefore, whether enrolled in a trial or not, ICU patients are particularly likely to experience clinical events that fall within the definition of a serious adverse event. These events include death, nosocomial infection, and laboratory test results indicating potentially dangerous physiologic abnormalities. Thus, a high proportion of ICU patients may experience a serious adverse event.

We clearly described the SAEs we plan to identify and label these as primary and secondary outcomes. These outcomes will be reported in the CRF and do not have to be reported separately. Periodic reports of SAEs will be reported through an Internet portal for submission, review, registration, and publication of medical research involving human subjects, to the accredited MREC that approved the protocol and the safety committee. Since case fatality in the patient population under study is known to be around 50%, a line listing of patients that have met the primary endpoint including deaths will be performed, with reporting once per 3 months. This reporting will be the responsibility of the study coordinator and the primary investigator. Other SAE’s then the outcome measures can be spontaneously reported in the CRF if serious and possible occur as a consequence of the study and will also be included in the 3 monthly line listing report.

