### Eligibility criteria {10}

All adults receiving ECMO treatment at the ICU of one of the participating centers during the study period are eligible for inclusion.

The exclusion criteria are as follows: (1) patients in whom the ECMO is only used to bridge a procedure like a high-risk percutaneous coronary intervention or during surgery; (2) no (deferred) informed consent; (3) vital indication for robust anticoagulation (e.g., mechanic mitral valve, pulmonary embolism, a clot in the cardiac ventricle); and (4) a history of heparin-induced thrombocytopenia (HIT).

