#### Intervention description {11a}

Eligible patients will be randomized in a 1:1:1 ratio between three anticoagulation strategy’s during ECMO therapy: (1) UFH with a target of 2–2.5× baseline aPTT (usual care, about 60–75 s), (2) UFH with a target of 1.5–2.0× (45–60 s), and (3) therapeutic dosage LMWH guided by weight and renal function. Adjustment of heparin and dosage of LMWH will be done according to the local anticoagulation protocols of the participating centers. After the start of ECMO timing of anticoagulation administration will be done according to usual care, so maybe postponed in case of postoperative bleeding for up to 24 hours. No additional invasive procedures are performed in the course of this research. Only laboratory or radiological tests that are part of routine medical treatment will be obtained if relevant.

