#### Criteria for discontinuing or modifying allocated interventions {11b}

Crossover to another treatment arm than allocated is allowed based on any of the following: (1) meeting one of the components of the primary outcome, (2) an acquired vital indication for high therapeutic anticoagulation, and (3) additional laboratory results that point towards a strong risk for coagulation disorder or hypercoagulation. Crossover to another treatment than allocated is in principle temporary. The timing of reversion is left to the consideration of the treating physician. The crossover will be mentioned in the case report form (CRF) and the primary and secondary outcome parameters will be measured and mentioned in the CRF after crossover as well.

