### Outcomes {12}

The primary outcome parameter of this study is a composite endpoint consisting of (1) severe hemorrhagic complications according to the ELSO definitions: clinically overt bleeding with a transfusion requirement of more than 20 ml/kg red blood cell (RBC) transfusions or >3U RBC in one calendar day. Bleeding that is retroperitoneal or pulmonary or involves the central nervous system or bleeding that requires surgical intervention will also be considered major bleeding; (2) severe thromboembolic complication defined as ischemic stroke, limb ischemia, or acute pump failure; (3) mortality at 6 months. This composite outcome was designed to capture the net clinical effect of reduced anticoagulation targets, e.g., a reduction of major bleeding not counteracted by an increase in thromboembolic complications. Mortality is part of the composite outcome to capture unknown or unmeasured effects of reduced anticoagulation.

Secondary endpoints are all other variables that may be affected by the anticoagulation regime: (1) blood transfusions, (2) quality of life (HR-QoL) at 6 months, (3) exchange of the membrane oxygenator, (4) vessel thrombosis after ECMO removal detected by echography, (5) pulmonary embolism, (6) costs, (7) the individual components of the composite outcome, (8) all thromboembolic complications combined, and (9) all hemorrhagic complications combined.

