## Assignment of interventions: blinding

### Who will be blinded {17a}

In this single-blind open-label study, only the patient will be blinded for the allocation. Outcome assessment and statistical analysis will be done blinded for treatment allocation.

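### Serious adverse events outside the outcome list are reported optionally and only if staff who know the arm think the study may have caused them, so harms such as new HIT may be under-recorded, and unequally between arms

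*Protocol article*

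**What the plan says.** Under Adverse event reporting and harms {22}, the article first notes that SAEs are common in this ICU population. It then restricts planned collection to the outcomes: "We clearly described the SAEs we plan to identify and label these as primary and secondary outcomes". For these, "These outcomes will be reported in the CRF and do not have to be reported separately". For the rest, SAEs other "then the outcome measures can be spontaneously reported in the CRF if serious and possible occur as a consequence of the study", after which they join the three-monthly line listing.

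The outcomes are listed under Outcomes {12}. The primary composite covers major bleeding, severe thromboembolic complications and death. The nine secondary items end with "7) the individual components of the composite outcome, (8) all thromboembolic complications combined, and (9) all hemorrhagic complications combined". New HIT is not among them. HIT appears only as an exclusion under Eligibility criteria {10}: "a history of heparin-induced thrombocytopenia (HIT".

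The control arm is described under Intervention description {11a} as "UFH with a target of 2–2.5× baseline aPTT (usual care, about 60–75 s". The other arms give UFH at a lower target and LMWH. On blinding, section {17a} says that "only the patient will be blinded for the allocation". It adds that outcome assessment and analysis are done blinded, but does not mention SAE reporting. Data management {19} has the local investigator or research nurse enter the data.

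**The concern.** The sentence on other SAEs contains two filters. One is discretion: the event may be reported but need not be. The other is causality: it must be thought a possible consequence of the study, which is not the same as a consequence of the anticoagulant. The people applying both filters know the arm.

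That combination matters because one arm is labelled usual care. A clinician can reasonably think that an adverse event on usual-care UFH would have happened without the trial and so falls outside the rule. The same clinician can think that the same event on a strategy assigned only because of the trial falls inside it.

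At stake are the safety data outside the composite. The safety committee is asked to look for evidence of harm and may advise stopping some arms. For non-outcome SAEs, the only stated route to it is this filtered one. The gap is easy to see for HIT. The Outcomes section introduces its secondary list as covering everything else that the anticoagulation regimen could influence, yet a heparin-specific harm that the protocol itself names is left to spontaneous reporting.

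**Working it through.** No figure in the document bears on this point, so there is none to reproduce. The check is a comparison of sections, followed by an illustration with assumed values.

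**Sections side by side**

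1. *Is reporting of other SAEs required?* No. Section {22} permits it and makes it conditional on a possible link to the study.
2. *Is new HIT an outcome, and so exempt from the filter?* No. It is in neither the composite nor the nine secondary items.
3. *Can HIT occur in every arm?* All three arms give a heparin (section {11a}), and section {10} treats a history of HIT as a reason to exclude.
4. *Do those applying the filter know the arm?* Yes. Only the patient is blinded (section {17a}) and site staff enter the data (section {19}). Blinded outcome assessment does not help here, because these events are not outcomes.
5. *Does the rule differ by arm?* No. The sentence is the same for every patient. Unequal recording is a risk that follows from points 1 and 4 and the usual-care label; it is not a stated rule.
6. *Where is the contrast sharpest?* Between usual-care UFH and LMWH. The reduced-target arm receives the same drug as control, so HIT there is less obviously attributable to the study.

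**Illustration (all rates assumed)**

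Patients per arm: 330 / 3 = 110. Let the true event rate be *p*, and let *r* be the proportion of events that are recorded.

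- Expected recorded events in an arm = 110 × *p* × *r*.
- With the same *p* in both arms, the recorded ratio (intervention / usual care) = *r* (intervention) / *r* (usual care). It does not depend on *p*.

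With *p* = 5% there are 110 × 0.05 = 5.5 true events per arm:

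| Recorded in usual care | Recorded in intervention arm | Expected recorded events | Ratio |
|---|---|---|---|
| 100% | 100% | 5.5 vs 5.5 | 1.0 |
| 50% | 90% | 2.75 vs 4.95 | 1.8 |
| 20% | 80% | 1.1 vs 4.4 | 4.0 |

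With *p* between 2% and 10% the ratios are the same, and the true count runs from 2.2 to 11 per arm. The table shows only how the filter would carry through to a listing. The ratios restate the assumed recording proportions and are not evidence that recording will differ. With so few events, the counts would be imprecise even if recording were complete.

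**The case against.** The strongest defence has five parts.

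- *The rule is the same for all arms, and usual-care UFH is itself a randomised allocation.* An investigator may read a consequence of the study as a consequence of the allocated anticoagulant. This stands. A reader might infer that the filter makes recording differ between arms of necessity. The text does not support that: it creates the opportunity, not the fact.
- *Selective collection is a deliberate choice, with a stated reason.* Background SAE rates in the ICU are high. This stands as a reason for not collecting everything. It does not explain why a short list of anticoagulant-related harms should be optional.
- *Much is captured anyway.* Stroke, limb ischemia, pulmonary embolism, other thromboembolic events, bleeding, transfusion and death are collected in every arm, so the thrombotic consequences of HIT would be seen. The article describes no between-arm test of other SAEs. All of this stands and limits the reach of the point.
- *There is monitoring.* Section {23} has an independent monitor check for missed SAEs. This is a partial safeguard only: visits may be as few as one per site per year, source verification covers a selection of patients, and an event whose reporting is optional is hard to class as missed.
- *This is a condensed article.* The full protocol or CRF may contain a HIT field. That is possible, and silence on such a field is not the criticism. The point rests on the reporting rule that the article states.

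A reader might also see a contradiction between the HIT exclusion, the reporting rule and the crossover text ("Crossover to another treatment arm than allocated is allowed based on any of the following"), since every arm is a heparin. There is none. One section governs entry, one reporting and one moves between arms, and section {11d} leaves usual care pathways in place.

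**Conclusion.** The point holds as a risk. As written, SAEs outside the outcome list are reported at the discretion of staff who know the arm, and only if they suspect a link to the study. Such harms may be under-recorded everywhere and may be recorded unequally, most clearly between usual-care UFH and LMWH. If events in usual care were the ones missed, the intervention arms would look worse than they are, or a true excess on usual-care UFH would be hidden.

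The size is unknown. The document gives neither a HIT rate nor a recording proportion, so a several-fold distortion should not be inferred from the illustration. The primary endpoint and the main non-inferiority conclusion are not touched. The conclusion assumes that sites follow section {22} as worded and that no fuller rule in an unseen document overrides it. On that footing, this is a cheap and worthwhile improvement to the safety data, not a threat to the trial's main result.

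**What to change.** In Adverse event reporting and harms {22}, replace the optional wording for other SAEs as follows:

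- Set a short fixed list of anticoagulant-related SAEs, including routinely diagnosed HIT (yes/no, with date). Record it from the medical file for every patient in all three arms, whatever the perceived relation to the study.
- Keep the relatedness judgement as a separate field, so that it no longer decides whether an event is recorded.
- Show the listed events by arm in the safety committee's report, prepared so that the steering committee stays blinded as section {21a} intends.

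The cost is a few CRF fields, a wording change and a small amount of extra data entry. No test is added, because only routinely diagnosed events are recorded. According to Trial status, 111 of 330 patients had been recruited at the time of the article. Those 111 would need retrospective entry from their files, and the remaining 330 − 111 = 219 could be recorded prospectively.
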